### Data collection

Collection of outcome data will be integrated into both the intervention and control group websites and will be collected at baseline (prior to completion of the intervention) and 3-, 6-, and 12-months post-intervention. At each study visit, participants in both groups will complete self-report measures of mental health, decisional conflict, use of safety actions, self-efficacy for safety planning, social support, mastery, IPV severity and coercive control. Demographic information will be collected at baseline and updated at subsequent waves, if needed. Website utilization data for both study arms will be collected automatically to track the number of times the site is accessed, time spent, and materials accessed and skipped. This information will be used to describe how women engage with the intervention and control websites (including completion rates of specific sections). Feedback on the helpfulness of the online intervention will also be collected at the end of each study session. Women will be asked to complete a brief exit survey immediately following the 12-months study visit to gather their ratings of perceived comfort, harms and benefits of the research using questions adapted from other studies, and any additional comments they wish to provide.

### Statistical analysis

#### Examination of outcomes by study arm

The effectiveness of the intervention will be assessed by comparing the intervention and control groups on changes in outcome measures, between the baseline and the 3, 6, and 12 month post-baseline assessments. We will test the hypothesis that, at 3, 6 and 12 months post-baseline, the intervention group will have improved mental health (our primary outcomes), in comparison to the control group, using intent-to-treat principles with generalized estimating equations (GEE). The same approach will be used for testing secondary outcomes which hypothesize decreased decisional conflict, increased safety seeking behavior, mastery and self-efficacy. Separate analyses will be conducted for each outcome. The parameter of interest is the group (intervention vs. control) by time interaction, which if significant means that change over time differs for intervention and control groups. Significant findings will be graphed to determine the nature of the effect. Potential confounding variables for which intervention and control groups are significantly different at baseline and variables that are related to missingness will be entered in the model. These analyses will establish overall effect sizes, for specific outcomes, for the intervention.

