### Objectives of the trial

The primary aim of this study is to test the effectiveness of *iCAN,* a tailored, online safety and health intervention, in improving the health and safety actions of adult women experiencing IPV. A group of women completing *iCAN* will be compared to a control group who receive general online safety information as a proxy for usual care. We hypothesize that, compared to the control group, women in the intervention group will: 1) have reduced symptoms of depression and PTSD (primary outcomes), and increase self-efficacy for safety planning, use of helpful safety actions, and mastery (secondary outcomes) at 6 and 12 months post-baseline; and 2) reduced decisional conflict immediately post-baseline (after completing the intervention one time) and at 6 and 12 months post-baseline. Additional aims are to: a) describe how women engage with the intervention, and their perceptions of its strengths and weaknesses; b) examine whether repeat engagement or dose are related to intervention effects; c) explore whether specific groups of women benefit in more or different ways from the intervention than others; and, d) examine the processes of change that explain how any positive outcomes are achieved.

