## Methods

### Trial design

A two arm, double-blind randomized controlled trial is being conducted to test the effectiveness of *iCAN* in a diverse sample of Canadian women who are experiencing IPV. The protocol was developed using CONSORT e-health guidelines [31]. Outcomes will be measured pre-intervention (baseline) and 3, 6 and 12 months post-intervention; decisional conflict will also be measured immediately post-intervention (after a single completion of the intervention). Website utilization data are being collected to capture access to and use of the intervention and control conditions. Women’s experiences of engaging with the intervention and control condition will be explored after completion of the 12-month study visit using their ratings of potential benefits and harms and comments about their experiences (collected online) and via in-depth qualitative interviews conducted with a sub-sample of approximately 60 women. Ethics approval for this study was obtained in July 2014 from the Institutional Research Ethics Boards at the University of Western Ontario, University of British Columbia, and University of New Brunswick.

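### The Objectives place the primary hypothesis at 6 and 12 months, but the analysis tests a group-by-time interaction over 3, 6 and 12 months, which can be significant without supporting it

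*Protocol article*

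**What the plan says.** Under Objectives of the trial, hypothesis 1 is directional and tied to visits. The intervention group will "have reduced symptoms of depression and PTSD (primary outcomes"), and will "increase self-efficacy for safety planning, use of helpful safety actions, and mastery (secondary outcomes) at 6 and 12 months post-baseline". Hypothesis 2 adds decisional conflict, immediately after baseline and again at 6 and 12 months. Trial design confirms that "decisional conflict will also be measured immediately post-intervention (after a single completion of the intervention").

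Under Examination of outcomes by study arm, the primary hypothesis has other visits: "We will test the hypothesis that, at 3, 6 and 12 months post-baseline, the intervention group will have improved mental health (our primary outcomes"). The test is then named: "The parameter of interest is the group (intervention vs. control) by time interaction, which if significant means that change over time differs" between the arms. The next step is: "Significant findings will be graphed to determine the nature of the effect". Secondary outcomes, including decisional conflict, are to be analysed in the same way, and the only visits listed are baseline, 3, 6 and 12 months.

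**The concern.** The document gives two versions of its primary hypothesis, one with month 3 and one without. An analysis plan cannot follow both.

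The named parameter is also not tied to the visits in the Objectives. A group-by-time interaction asks whether the two trajectories differ in any way. How far that is from a difference at 6 and 12 months depends on how time is coded, which the article does not say:

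- **Categorical time.** With four visits the interaction has 3 degrees of freedom. A difference confined to month 3 can make it significant.
- **Linear time.** The interaction is a difference in slopes. A benefit that appears by month 3 and then stays constant is poorly described by a slope.

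At stake is what a positive primary result would mean. A reader of the Objectives would take it as benefit at 6 and 12 months, and the stated rule does not guarantee that. Separately, the immediate decisional-conflict assessment is hypothesised and measured but appears in no listed analysis.

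**Working it through.** **The plan's own figure.** Number of participants required states power of .73 for depression and .92 for PTSD with 400 women, alpha .05 and a 15% greater change, based on repeated measures ANOVA. This cannot be rebuilt, because the means, SDs, correlation and contrast are not printed. A plain two-sided two-sample comparison with 200 per arm gives .826 at an effect size of 0.29. What follows does not depend on those power figures. They are used only to choose a plausible effect: power .73 in a plain two-sample test corresponds to (1.960 + 0.613)/√(200/2) = 0.257 SD.

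**Inputs.** From the article: 200 per arm, alpha .05 (taken as two-sided), visits at 0, 3, 6 and 12 months. Assumed: SD 1, compound symmetry, correlation ρ from 0.4 to 0.7, complete data, no difference at baseline. Benefit is scored as positive.

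**Formulas.** Let δ be the four between-arm differences and n = 200.

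- 3-df interaction: noncentrality λ = n/[2(1−ρ)] × Σ(δ − mean δ)², referred to a noncentral chi-square with 3 df.
- Linear slope: centred times are −5.25, −2.25, 0.75 and 6.75, with sum of squares 78.75. z = (Σ centred time × δ / 78.75) / √[2(1−ρ)/(n × 78.75)].
- Contrast of the 6- and 12-month average minus baseline: weights (−1, 0, ½, ½), sum of squares 1.5. z = contrast / √[1.5(1−ρ) × 2/n].

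**Worked at ρ = 0.5.**

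- Month 3 only, δ = (0, 0.257, 0, 0). Σ(δ − mean δ)² = 0.75 × 0.257² = 0.0495, so λ = 200 × 0.0495 = 9.91 and the interaction rejects in 76%. The 6/12-month contrast is zero and rejects in 5%. The slope has z = (−2.25 × 0.257/78.75)/0.00797 = −0.92 and rejects in 15%, pointing in the unfavourable direction.
- Constant from month 3, δ = (0, 0.257, 0.257, 0.257). λ is again 9.91, power .76. Slope z = (5.25 × 0.257/78.75)/0.00797 = 2.15, power .58. Contrast z = 0.257/0.0866 = 2.97, power .84.
- 6 and 12 months only, δ = (0, 0, 0.257, 0.257). Σ(δ − mean δ)² = 0.257² = 0.0660, so λ = 13.2 and power is .88, against .84 for the contrast.

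**Proportion of trials significant, over the assumed range of ρ:**

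| True pattern (0.257 SD) | Test | ρ 0.4 | 0.5 | 0.6 | 0.7 |
|---|---|---|---|---|---|
| Month 3 only | 3-df interaction | .67 | .76 | .85 | .94 |
| | Linear slope | .13 | .15 | .18 | .22 |
| | 6/12-month contrast | .05 | .05 | .05 | .05 |
| Constant from month 3 | 3-df interaction | .67 | .76 | .85 | .94 |
| | Linear slope | .50 | .58 | .67 | .79 |
| | 6/12-month contrast | .77 | .84 | .91 | .97 |
| 6 and 12 months only | 3-df interaction | .80 | .88 | .94 | .985 |
| | 6/12-month contrast | .77 | .84 | .91 | .97 |

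With 0.29 SD, an effect size the article itself prints, the pattern is the same. A month-3-only difference is significant in .78 to .98 with the 3-df test. For a constant benefit the slope has power .60 to .88 and the contrast .86 to .99.

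**The case against.** The best defence is that the analysis section opens by comparing the arms on change from baseline to each of the three follow-up visits. If time is categorical with baseline as reference, the interaction coefficients are exactly those visit-specific differences, each with a sign and a standard error. The section also promises effect sizes. A group-by-time interaction is a standard test for repeated outcomes, and time coding and exact contrasts are commonly left to a statistical analysis plan that is not shown here. Under the analysis section's own version of the hypothesis, a month-3 benefit is relevant.

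Much of this stands. The needed estimates would be available from such a model, and the absence of coding detail is not itself a fault. What remains is in the printed text: two conflicting sets of visits, and significance of the whole interaction as the named parameter, with no visit attached.

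A reader might infer more, and the documents do not support it:

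- *That the graph replaces the test.* The inference is the GEE interaction. The graph comes afterwards, to interpret a significant result.
- *That a 6/12-month benefit is generally diluted.* When the effect appears only at 6 and 12 months, the 3-df interaction is slightly stronger than the contrast (.88 against .84 at ρ 0.5).
- *That both problems arise together.* The month-3-only problem needs categorical time and the loss of power to the slope needs linear time.
- *That the stated .73 falls once 3 df are used.* The article does not say how many degrees of freedom lie behind .73.
- *That the interaction is faulty because harm would reject as often as benefit.* That is true of any two-sided test.
- *That the immediate decisional-conflict hypothesis is certain to go untested.* The assessment is planned and not excluded. It is simply not placed in the analysis.

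**Conclusion.** The point holds in this limited form. The Objectives and the statistical analysis section give different visits for the primary hypothesis, and the parameter named for testing it can be significant without any difference at 6 or 12 months. With categorical time, a month-3-only difference of 0.257 SD would be significant in 67% to 94% of trials. With linear time, a constant benefit would be tested with power .50 to .79, against .77 to .97 for a direct contrast. These sizes rest on assumed compound symmetry, ρ of 0.4 to 0.7 and complete data. The contradiction in visits rests on no assumption. The unplaced decisional-conflict assessment is a real but secondary mismatch. This should be fixed because it bears on what the primary result can claim, but it does not invalidate the design or the choice of GEE.

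**What to change.** - State the same visits for the primary hypothesis in the Objectives and in the statistical analysis section.
- Treat time as categorical. For each primary outcome, base the primary conclusion on one pre-specified between-group contrast in change from baseline at the hypothesised visits, for example the average of 6 and 12 months, with its estimate and 95% CI.
- Report the month-3 difference as secondary.
- Add a separate between-group contrast for decisional conflict at the immediate post-intervention assessment.
- Keep the graph as description, shown whether or not the test is significant.

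The cost is a change of analysis wording, with no new data. The article reports the trial as in active follow-up, so the change can be dated before the final analysis. The downside is that an effect seen only at 3 months could no longer be claimed as a primary result.

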### Number of participants required

A sample of 450 women (225 per group) will be recruited for this trial based on the statistical power needed to both test the impact of the tailored online intervention on primary outcomes using a general estimating equations (GEE) approach, and, subsequently, to examine mechanisms by which the intervention exerts its effects on these outcomes using Structural Equation Modeling (SEM). We based the power analysis on two key outcomes: decreased symptoms of depression, and of PTSD. Baseline means and standard deviations from the IRIS study [34], a similar trial in the USA, were used in the power analysis. In estimating the sample size, we varied the percent change over time in the intervention group relative to the control group from 15% to 20% which corresponds to moderate effects sizes, 0.29 and 0.52, found in previous studies of IPV interventions. The power analysis was based on repeated measures ANOVA since specific estimates of variance needed to calculate sample size for GEE are not available. However, in the GEE we will be able to retain all cases in the analysis, including those with missing data. With an alpha of .05, 15% greater change in the intervention group, relative to the control group, a sample size of 400 participants provides .73 power for depression and .92 power for PTSD. With a 20% greater change in the intervention, power is .94 for depression. We assume that attrition will be approximately 10%, based on the retention rate in the recently completed US trial (<10% at 12 month follow up) [35] and our recent success in retaining 81% of a cohort of women who had experienced IPV over a 4- year period. Attrition of 10% at 12 months would result in a final sample of 405 women, adequate for all analyses.

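### As most naturally read, the primary analysis is an unadjusted difference in change from baseline: valid, but less precise than a baseline-adjusted comparison of the same data

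*Protocol article*

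**What the plan says.** Under Examination of outcomes by study arm, the measure of effectiveness is given as: "comparing the intervention and control groups on changes in outcome measures, between the baseline and the 3, 6, and 12 month post-baseline assessments". The model is a GEE, fitted separately for each outcome, and its target is named thus: "The parameter of interest is the group (intervention vs. control) by time interaction, which if significant means that change over time differs". The only rule for covariates is conditional: "Potential confounding variables for which intervention and control groups are significantly different at baseline and variables that are related to missingness will be entered". The baseline value of the outcome is not named as a fixed covariate, and nothing is said about holding the baseline means equal.

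Under Number of participants required, the power calculation uses a different method from the analysis: "The power analysis was based on repeated measures ANOVA since specific estimates of variance needed to calculate sample size for GEE are not available". At the smaller effect, a 15% advantage in change with alpha .05, the plan reports: "a sample size of 400 participants provides .73 power for depression and .92 power for PTSD". For the larger effect it reports: "With a 20% greater change in the intervention, power is .94 for depression".

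**The concern.** Women are randomised and the baseline measures precede the intervention, so the true baseline means of the two arms are equal by design. A group-by-time model that gives each arm its own baseline mean does not use that fact. Its interaction terms are differences in mean change, so they carry the sampling error of the observed baseline difference in full. An analysis that regresses on baseline, or imposes a common baseline mean, removes only the part of that difference that predicts the follow-up score.

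The baseline score of every outcome is already collected, so the lost precision would be avoidable. It matters most for depression, one of the two primary outcomes, where the stated power at the lower effect is .73. The conditional covariate rule is no substitute. It makes adjustment depend on the observed baseline comparison or on missingness, whereas the gain comes from adjusting for a prognostic baseline score in every case.

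**Working it through.** **Inputs.** From the article: alpha .05; N = 400 (200 per arm); power .73 (depression, 15%), .94 (depression, 20%), .92 (PTSD, 15%). Assumed, because the article does not give them: a two-sided test; r, the correlation of baseline with follow-up; k, the follow-up SD divided by the baseline SD.

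**Can the plan's figure be reproduced?** No. The means, SDs and within-person correlation behind .73 are not printed. The plan ties its 15% to 20% range to effect sizes of 0.29 and 0.52, but a plain two-sample comparison with 200 per arm gives .83 at 0.29 and .999 at 0.52. The two stated depression powers do agree with each other. If .73 is the power of a 3-df group-by-time test at 15%, scaling the effect by 20/15 gives .943, against the stated .94. A 1-df test gives .929. So .73 behaves like the power of an unadjusted group-by-time test over all visits. This is an indication, not proof.

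**Variances for one follow-up visit**, in units of the baseline variance and leaving out the common factor for sample size:
- difference in change: k² + 1 − 2rk
- baseline-adjusted: k²(1 − r²)
- first minus second: 1 − 2rk + r²k² = (1 − rk)², which is never negative.

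The direction therefore does not depend on r or k; the two variances are equal only when rk = 1. With k = 1 the ratio is (1 − r²)/[2(1 − r)] = (1 + r)/2.

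**Power with k = 1.** Take .73 as the power of the difference-in-change test: z(.73) + 1.960 = 0.613 + 1.960 = 2.573. After adjustment, power is Φ(2.573/√ratio − 1.960).

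| r | ratio | depression, from .73 | PTSD, from .92 | N giving the same power as 400 |
|---|---|---|---|---|
| .5 | .75 | .84 | .97 | 300 |
| .7 | .85 | .80 | .95 | 340 |
| .8 | .90 | .77 | .94 | 360 |

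A simulation with complete data, 200 per arm and 4,000 runs compared the 12-month change score with a baseline-adjusted analysis. It gave .72 against .83 at r = .5, and .73 against .79 at r = .7, in line with the table.

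**Power with k = 1.2** (follow-up scores more variable than baseline).
- r = .5: ratio = 1.44 × .75 / (2.44 − 1.20) = 1.08/1.24 = .871. Power = Φ(2.573/√.871 − 1.960) = .79.
- r = .7: ratio = 1.44 × .51 / (2.44 − 1.68) = .734/.76 = .966. Power = .74.

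The variance reduction falls from 25% to 13% at r = .5, and from 15% to 3% at r = .7.

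**Several visits.** Take .73 as the power of the 3-df test, with equal correlations between all visits, equal SDs and the same effect at each follow-up. Baseline adjustment then gives .92, .84 and .80 at r = .5, .7 and .8.

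**The case against.** The strongest objection is that the article writes out no model. It gives no coding of time and no statement about baseline means. A model with a common baseline mean also tests its effect through group-by-time terms, so the sentence on the parameter of interest does not rule out the efficient analysis. A condensed article may leave this to a statistical analysis plan that is not shown. This stands in part: a reader might take it as established that each arm has its own baseline mean, and the text does not establish that. It is the natural reading because of three things together: the comparison of changes, the power calculation by repeated measures ANOVA, and a covariate rule that is only conditional.

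Second, difference in change is a standard and valid analysis of a randomised trial. That stands fully. A reader might infer bias or an invalid test, and nothing in the article supports that.

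Third, the size of the gain rests on an unstated correlation, on equal SDs and on a single-visit contrast, and it is carried from an ANOVA power figure to a GEE. This also stands. At k = 1.2 and r = .7 almost nothing is gained, while a multi-visit test gains more. No single figure should be quoted as the power lost.

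Fourth, quoting .73 alone would be selective. A reader might conclude that the trial as a whole is underpowered, but .73 belongs to one outcome at the lower of two effects.

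**Conclusion.** The point holds as one of efficiency. As most naturally read, the plan estimates an unadjusted difference in change, and in large samples a baseline-adjusted or common-baseline-mean analysis is at least as precise whatever the correlation and SDs. For depression at the 15% effect, the single-visit gain takes .73 to between .77 and .84 for r from .8 to .5 with equal SDs, and only to .74 to .79 for r from .7 to .5 with an SD ratio of 1.2. A test over all three visits would gain more under the assumptions shown. These figures take the stated .73 as the power of the unadjusted test, with a two-sided alpha and complete data. The documents do not support a claim of bias, certainty that the baseline means are left free, or a fixed size of loss. If the sponsor already constrains or adjusts for baseline, one clarifying sentence settles the matter.

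**What to change.** Prespecify one of two models for every outcome measured at baseline, whatever baseline differences are observed:

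1. the 3-, 6- and 12-month scores as responses, with the baseline score and its interaction with visit as covariates; or
2. baseline kept as a response, with one common baseline mean for both arms and arm differences only after baseline. This form keeps women who have a baseline score alone in the model, in line with the plan's aim of retaining all cases. In a GEE it needs a working correlation other than independence, because under independence the baseline score brings no gain.

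Report the adjusted between-arm differences at the planned follow-up visits, not at 12 months alone: the objectives name 6 and 12 months, and the analysis section names 3, 6 and 12.

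The trial is in active follow-up and the statistician is not blind to allocation, so the choice should be dated and documented before any comparison of outcomes by arm. The cost is a model specification; no further women, visits, data or software are needed.
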